Given the multifactorial nature of LBD, factors other than the pathoanatomical source of pain also need to be considered in a robust classification approach [12], including neurophysiological [21,22] and psychosocial components of LBD [23,24]. The duration of injury is also considered an important factor in the presentation and prognosis of people with LBD [24-26]. We are interested in investigating specific physiotherapy treatment strategies in the subacute population of LBD, where spontaneous recovery is less rapid and the complex issues associated with chronic pain are less likely to be fully entrenched [4,6,27]. In the context of such a population, we have developed specific treatment protocols for five LBD subgroups that consider pathoanatomical, neurophysiological and psychosocial mechanisms. The five subgroups are i) lumbar disc herniation with associated radiculopathy ([name], [name], [name]: A classification and treatment protocol for low back disorders: Part 3- Functional restoration for intervertebral disc related problems, submitted); ii) reducible discogenic pain ([name], [name], [name]: A classification and treatment protocol for low back disorders: Part 2- Directional preference management for reducible discogenic pain, submitted); iii) non-reducible discogenic pain ([name], [name], [name]: A classification and treatment protocol for low back disorders: Part 3- Functional restoration for intervertebral disc related problems, submitted); iv) zygapophyseal joint dysfunction [28] and; v) multi-factorial persistent pain ([name], [name], [name]: A classification and treatment protocol for low back disorders: Part 4- Functional restoration for multi-factorial persistent pain, submitted). These five subgroups have been chosen based on i) their common recognition by clinicians [29-31]; ii) their description in another pathoanatomical classification system [15,32] and; iii) significant evidence of subgroup reliability and validity [15,32,33].

A randomised controlled trial is planned to evaluate the effectiveness of the subgroup-specific treatment. Advice will be the comparison intervention as it is recommended in all international guidelines for the management of LBD [34] and has demonstrated efficacy in randomised controlled trials [35-37].

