### Eligibility and screening

Participants will be sought via newspaper advertising, public notices, and via referral from medical practitioners and physiotherapists. Potential participants will initially undergo a preliminary screening for eligibility via telephone. These initial selection criteria are common to all subgroups and are outlined in Table 1. Those found to be potentially eligible will be invited to attend a physical examination with one of the treating physiotherapists. The physical examination will i) confirm eligibility; ii) determine which subgroup (if any) the participant fits and; iii) provide descriptive information on the baseline characteristics of participants. The physical examination will involve:

**Table 1 T1:** Eligibility criteria common to all subgroups

Inclusion criteria
1. A primary complaint of either: a. low back pain, defined as pain between the inferior costal margin and the inferior gluteal fold with or without referral into the leg(s) [138,139], or b. referred leg pain, defined as predominately unilateral posterior leg pain extending below the knee, or anterior thigh pain, with or without back pain (disc herniation with associated radiculopathy subgroup only) [56]
2. Duration of current episode of primary complaint lasting between 6 weeks and 6 months (subacute stage of injury [27,140]), with at least a 4 week pain-free period separating the current episode from any previous episodes [141,142]
3. Aged between 18 and 65 (inclusive)
4. Fluency in English sufficient to complete questionnaires and to enable understanding of the intervention
5. Classified into one of the five subgroups of low back disorders being targeted in the trial
6. Agreeing to refrain from other interventions wherever possible for the 10-week treatment period of the trial, aside from consultations with medical practitioners, medication, and any exercises already being undertaken

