### Data analysis

Data analysis will focus on detecting the between-group treatment effect (with 95% confidence intervals) at each of the follow-up points (5 weeks, 10 weeks, 26 weeks and 52 weeks following randomisation). Analyses will be conducted using PASW Version 18^b^, with alpha set at 0.05 using a two-tailed hypothesis. Continuous data will be analysed using linear mixed models (with the group x time interaction estimating the treatment effect). These were chosen for their strength in analysing longitudinal biological data and accounting for correlations associated with repeated measurements [104-106]. The mixed models will adjust for the baseline score of the outcome of interest, along with the stratification variables (treatment centre and subgroup) as recommended by the revised CONSORT statement [107]. The inclusion of treatment centre as a random effect will account for the potential clustering of outcomes within treatment centres [108,109]. In addition, the mixed models will adjust for gender and Orebro Musculoskeletal Pain Questionnaire score, as gender and psychosocial factors are considered to be important prognostic factors [107]. Ordinal data will be analysed using the Mann Whitney U test.

At each follow-up point, participants in each group will be dichotomised according to whether they achieved the minimum clinically important difference of the outcome or not, and then the risk ratio, risk difference and number needed to treat will be calculated along with 95% confidence intervals [107,110]. Statistical significance will be evaluated using Chi square analysis. For these purposes, the minimum clinically important difference will be defined as 10/100 for the Oswestry [111], 2/10 for the NRS pain scales [111], at least "much improved" on the global rating of change scale [71,112] and "very satisfied" on the treatment satisfaction scales [71]. It has been argued that these values for minimum clinically important difference may be too low in some contexts [113], hence we will repeat this analysis using a threshold of 50% reduction in Oswestry scores and NRS pain scores based on empirical validation studies suggesting that this may be a more suitable threshold for important differences [67,114].

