### Sample size

We will recruit a total sample size of at least 250 participants. We would require 128 participants (64 in each group) to detect the minimum clinically important difference between groups of 10% on the Oswestry assuming a standard deviation of 20 (two tailed hypothesis, alpha = 0.05, power = 80%) [120]. However, we wish to recruit more than this to improve power in our planned subgroup analyses. We acknowledge that the subgroup analyses are likely to remain underpowered [121], but they may provide some guidance for future research targeting the subgroups with greatest feasibility and effectiveness.

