## Discussion

In this randomised controlled trial we aim to compare specific physiotherapy treatment to advice in people with LBD classified into five subgroups. We hypothesise that participants who receive specific physiotherapy treatment according to their subgroup will achieve superior clinical outcomes to those who receive physiotherapy advice. We will be testing this hypothesis in participants with subacute, non-compensable LBD. This decision has been made to avoid inclusion of participants with negative prognostic indicators including chronic symptoms [6,122,123] and compensable injuries [124,125], as these participants may require more extensive intervention than either of the treatment arms offer in our trial. We will avoid including participants with acute symptoms as this may lead to difficulty in demonstrating treatment effects above the higher rate of initial spontaneous recovery that might be expected in these participants [4,6,7,27]. Importantly, there has been limited research into the management of subacute LBD [27], and developing effective treatments for this group represents an opportunity to prevent the transition to chronic symptoms [126].

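### Symptom duration meets the plan's own criterion for a covariate but is left out of the mixed models; adding it is a near-free, optional precision gain for the whole-trial analyses

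*Protocol article*

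**What the plan says.** The Data analysis section fixes the covariates of the linear mixed models: the baseline value of the outcome, treatment centre (as a random effect) and subgroup. It then states that "the mixed models will adjust for gender and Orebro Musculoskeletal Pain Questionnaire score", and justifies these last two by their importance for prognosis. Duration of the current episode is not listed.

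Elsewhere the article treats duration as prognostic. The Background states: "The duration of injury is also considered an important factor in the presentation and prognosis of people with LBD". Inclusion criterion 2 in Table 1 requires "Duration of current episode of primary complaint lasting between 6 weeks and 6 months", so duration has to be established for everyone before randomisation. The Discussion explains the restriction to subacute cases partly as a way to avoid "negative prognostic indicators including chronic symptoms". Under Randomisation and allocation, the strata are subgroup and centre only.

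**The concern.** The plan states a criterion for covariates beyond the baseline score and the stratification variables, namely prognostic importance, and applies it to gender and Orebro score. Duration meets the same criterion in the article's own words, but it is neither a stratification factor nor a covariate, and the omission is not explained. The eligible window is still wide: 6 weeks to about 26 weeks, or 26/6 = 4.3-fold.

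What is at stake is precision. In a linear model, adjusting for a baseline variable that predicts the outcome narrows the interval for the treatment effect. If duration predicts outcome within the window, the intervals for the Oswestry and the two pain scales could be somewhat narrower with no new visits or participants.

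**Working it through.** **Inputs from the protocol article.** Data analysis: "with alpha set at 0.05 using a two-tailed hypothesis". Sample size: a "minimum clinically important difference between groups of 10% on the Oswestry", "assuming a standard deviation of 20", 80% power, 128 required (64 per group), at least 250 planned. I take 250 as 125 per arm.

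**Assumed.** The partial correlation r of duration with the outcome, given the covariates already listed, is not in the documents. I use 0.1 to 0.3 and also find the break-even value. The whole-trial model is taken to have about 10 parameters, so one more covariate moves the residual degrees of freedom from 240 to 239.

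**1. Reproduce the plan's figure.**
n per arm = 2 × (1.960 + 0.842)² × (20/10)² = 62.8, so 63 (126 in total) by the normal approximation. The t-test calculation gives 63.77, so 64 per arm and 128 in total. The stated figure reproduces. It uses the full SD of 20 and takes no credit for any covariate, so it does not depend on whether duration is included.

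**2. Precision without duration.**
SE = 20 × √(2/125) = 2.530. The 95% CI half-width is 1.96 × 2.530 = 4.96 Oswestry points. Power for 10 points is Φ(10/2.530 − 1.96) = Φ(1.99) = 97.7%.

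**3. Precision with duration, whole trial.**
SE multiplier = √[(1 − r²) × 240/239].

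| r | SE multiplier | Fall in SE | CI half-width (points) |
|---|---|---|---|
| 0 | 1.002 | none (rises 0.2%) | 4.97 |
| 0.1 | 0.997 | 0.3% | 4.94 |
| 0.2 | 0.982 | 1.8% | 4.87 |
| 0.3 | 0.956 | 4.4% | 4.74 |

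Break-even: r² = 1 − 239/240 = 0.0042, so r is about 0.06.

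At r = 0.3 the SE is 2.530 × 0.956 = 2.418, and power for 10 points becomes Φ(10/2.418 − 1.96) = Φ(2.18) = 98.5%.

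If the planned covariates already explained 40% of the variance (assumed), the half-width without duration would be 3.84. At r = 0.3 it would become 3.84 × 0.956 = 3.67. The proportional change is the same and the absolute change smaller.

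**4. Single-subgroup models.**
The article gives no subgroup sizes. Five equal subgroups would give 50 each, or 25 per arm (illustrative). With baseline score, gender and Orebro already fitted, the expected SE multiplier for one more covariate is √[(1 − r²) × 44/43].

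- r = 0.1: √(0.99 × 1.0233) = 1.006, a rise of 0.6%.
- r = 0.2: √(0.96 × 1.0233) = 0.991, a fall of 0.9%.
- r = 0.3: √(0.91 × 1.0233) = 0.965, a fall of 3.5%.
- Break-even: r² = 1 − 43/44 = 0.0227, so r is about 0.15.

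**The case against.** The strongest reply is that nothing here is stated wrongly. The plan pre-specifies a reasoned covariate set, does not claim to list every prognostic factor, and deals with duration by restricting entry. The Background sentence is about low back disorders in general and leads into the choice of a subacute sample; the Discussion explains why chronic and acute cases are kept out. Neither says that duration predicts outcome between 6 weeks and 6 months. Restricting a variable's range usually weakens its correlation with outcome, and baseline score, subgroup and Orebro score may already carry part of its information. All of this stands. It limits the point to an unexplained difference in how the plan's own criterion is applied, with a gain that is assumed and not shown.

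A reader might infer more, in four ways that the documents do not support:

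- **Precision is certainly lost on every continuous outcome.** That needs a partial correlation which the article does not give and which may differ by outcome or be close to zero.
- **The omission biases the comparison.** In a linear model it does not: randomisation keeps the estimate unbiased, and the ordinary standard error already reflects chance imbalance in duration.
- **The trial is underpowered as a result.** The 128 uses no covariates, and 250 gives 97.7% power for 10 points without any.
- **The subgroup analyses would gain most.** The Sample size section concedes that they are underpowered, but at about 50 per subgroup the lost degree of freedom can cancel the gain, as step 4 shows.

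One practical limit also stands. The article shows that duration is ascertained for eligibility, but not that it is recorded in weeks.

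**Conclusion.** The point holds as an optional improvement. Duration satisfies the reason given for adding gender and Orebro score, has to be known before randomisation, and is omitted without explanation. Adding it to the whole-trial models would lower the standard error by roughly 0.3% to 4.4% if the partial correlation lies between 0.1 and 0.3. For the Oswestry that is a half-width of about 4.9 to 4.7 points instead of 4.96. Below a correlation of about 0.06 there is no gain.

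These sizes rest on the assumed correlations, the protocol's SD of 20, 125 per arm with complete data, and a model of about 10 parameters. The change is unlikely to alter the trial's conclusion. What favours it is the small cost.

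**What to change.** In the Data analysis section, add duration of the current episode at baseline (in weeks, if so recorded) to the pre-specified covariates of the whole-trial mixed models. The sponsor should confirm how the value is recorded. Make the change before any outcome data are analysed, including the preliminary analysis of two subgroups planned for thesis deadlines, so that the choice cannot look data-driven. If the investigators prefer to leave duration out, one sentence giving the reason would settle the inconsistency.

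Do not justify the change by the single-subgroup models.

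The cost is one phrase and one degree of freedom, about 0.2% in standard error if duration proves uninformative (√(240/239) = 1.002). If duration is already recorded for the eligibility check, no added data are needed; no added visits or participants are needed in any case.

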**Exclusion criteria**

1. An active compensation claim for their back injury, due to the negative influence that this can have on prognosis [125]
2. Active cancer under current treatment, as the treatment of the cancer may interfere with their ability to participate in the trial
3. Signs of cauda equina syndrome based on bladder or bowel disturbance and/or imaging [143]
4. Current pregnancy, or childbirth within the last 6 months, as this could impair ability to undertake exercises, and could also cause back and leg symptoms that are not related to the subgroups under investigation
5. Spinal injections within the last 6 weeks, as we wish to study treatment effects independent to the effects of injections [144]
5. Any history of lumbar spine surgery, as there is already considerable research evaluating the efficacy of post-surgical rehabilitation programs [145]
6. A pain intensity score of less than 2/10 on a 0-10 numerical rating scale due to low severity
7. Minimal activity limitation, evidenced by a baseline ability to walk, sit and stand for one hour or more and no sleep disturbance at night, as we wish to exclude people with low severity
8. Already received more than 5 sessions of physiotherapy with any of the treating physiotherapists prior to enrolment, as these therapists are likely to use many components of the trial treatment protocol on their usual client caseload
9. Inability to walk safely, such as severe foot drop causing regular tripping, as the interventions in the trial include walking for most participants
10. Planned absence of more than one week during the treatment period (such as overseas holidays)

• Observation of the spine for evidence of postural deformity such as a lateral shift or an increased or decreased lumbar lordosis [38], using protocols with acceptable reliability [39,40].

• Measurement of lumbar spine active movements into flexion, extension and lateral-flexion using finger-to-floor measurement methods that have been shown to be reliable [41].

• Lower limb neurological examination in a seated position, which will involve testing of knee jerk and ankle jerk reflexes, myotomal strength testing and dermatomal sensation in response to light touch with a tissue [42]. Acceptable reliability for these tests has been demonstrated in people with suspected lower limb nerve root compression [42].

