**Primary outcome measures**	
1. Oswestry Disability Index V2.1 with "sex life" question replaced by a "work/housework" question	0, 5, 10, 26, 52
2. Numerical rating scale for back pain (0-10)	0, 5, 10, 26, 52
3. Numerical rating scale for leg pain (0-10)	0, 5, 10, 26, 52

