#### Primary outcome measures

Activity limitation will be evaluated using nine questions from the Oswestry Disability Index version 2.1 [64], with the tenth question relating to "sex life" being replaced by a question relating to "work/housework" [65,66]. Rasch analysis has shown that this modified version performs as well as the original Oswestry [65], but it is aimed at preventing missing responses to the "sex life" question. The Oswestry has been shown to be a reliable, valid and responsive instrument for measuring activity limitation in people with low back pain and referred leg pain [67-69].

Separate 0-10 numerical rating scales (NRS) will be used to measure the average intensity of back pain and leg pain over the past week, with end-point descriptors of "no pain" and "worst pain possible" [70,71]. The NRS has good reliability [72,73], responsiveness [74,75] and validity [76,77].

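### The 2-point and 50% responder rules for back and leg pain cover all participants, including those whose baseline score on that scale is too low to respond

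*Protocol article*

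**What the plan says.** Leg pain and back pain are two of the three primary outcomes (Protocol article, Table 3 and Primary outcome measures). Separate 0-10 scales "will be used to measure the average intensity of back pain and leg pain over the past week", and the lower end of each scale means no pain, so 0 is a valid score.

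Table 1 sets who may enter. Inclusion criterion 1a accepts low back pain, defined as "pain between the inferior costal margin and the inferior gluteal fold with or without referral into the leg(s". Criterion 1b accepts referred leg pain, described in part as "or anterior thigh pain, with or without back pain (disc herniation with associated radiculopathy subgroup only". The Classification section requires leg symptoms in the radiculopathy subgroup only. The discogenic feature list makes leg pain optional, and the zygapophyseal and multi-factorial definitions do not mention it. The one pain floor, exclusion criterion 6, removes people with "A pain intensity score of less than 2/10 on a 0-10 numerical rating scale due to low severity" and does not say whether back or leg pain is meant.

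Under Data analysis, "participants in each group will be dichotomised according to whether they achieved the minimum clinically important difference of the outcome or not", at each follow-up, with risk ratio, risk difference, NNT and a chi-square test. The threshold for both pain scales is 2/10. The analysis is then repeated with "a threshold of 50% reduction in Oswestry scores and NRS pain scores". No minimum baseline is given for either rule, and the same section analyses all data by intention to treat.

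**The concern.** Someone with back pain only may score 0 for leg pain at baseline. Such a person has no leg pain to lose, yet enters the leg-pain responder analysis.

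Under the 2-point rule that person counts as a treatment failure in either arm, whatever the treatment does. Under the 50% rule the article gives no answer, because the percentage change is 0/0. The coding would have to be chosen later, possibly with results in view. A person going from 1 to 0 fails the first rule and passes the second, although the second was added because the first thresholds might be too low.

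At stake are the risk difference and the NNT, the figures that readers most readily apply to patients, and the power of the chi-square test. All three would depend partly on how many people without leg pain were enrolled.

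**Working it through.** **The plan's own figure.** Sample size gives 128 participants (64 per group) for a 10-point Oswestry difference, SD 20, two-sided alpha 0.05 and 80% power. The normal approximation gives 2 × (1.960 + 0.842)² × 20² / 10² = 62.8, so 63 per arm. The t-test gives 63.8, so 64 per arm. The figure reproduces, but it concerns the Oswestry only. The article gives no figure for the pain responder analyses.

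**Can a score of 0 or 1 occur?** If exclusion criterion 6 required at least 2/10 on both scales, it would contradict criteria 1a and 1b. If it refers to the main complaint, the other scale can still be 0. So low baselines are admitted, mainly for leg pain. For back pain, entry without it is possible only in the radiculopathy subgroup.

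**What the rules do**, reading the threshold as an improvement from baseline:

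| Baseline | 2-point rule | 50% rule |
|---|---|---|
| 0 | impossible | 0/0, undefined |
| 1 | impossible | met by 1 to 0 |
| 2 or more | possible | defined |

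**Size under the 2-point rule.** Let f be the share with a baseline below 2, the same in both arms, and let p₁ and p₀ be the response rates among the rest.

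- Observed rates: (1 - f)p₁ and (1 - f)p₀
- Risk difference: (1 - f)(p₁ - p₀)
- NNT: 1 / [(1 - f)(p₁ - p₀)]
- Risk ratio: p₁ / p₀, since (1 - f) cancels

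The documents give neither f nor the response rates. Assume p₁ = 60%, p₀ = 40% and 125 per arm (half of the planned minimum of 250). Restriction leaves 125 × (1 - f) per arm.

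| f | Risk difference, all | NNT, all | Risk ratio, all | Power, all | Power, restricted (per arm) |
|---|---|---|---|---|---|
| 0 | 20 points | 5.0 | 1.50 | 89% | 89% (125) |
| 20% | 16 | 6.3 | 1.50 | 74% | 81% (100) |
| 40% | 12 | 8.3 | 1.50 | 54% | 69% (75) |
| 60% | 8 | 12.5 | 1.50 | 35% | 52% (50) |

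Power is Φ[(d - 1.96·SE₀)/SE₁], where d is the risk difference, SE₀ uses the pooled rate and SE₁ the separate rates. For f = 40% and all participants, the rates are 36% v 24%:

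- SE₀ = √(2 × 0.30 × 0.70 / 125) = 0.0580
- SE₁ = √[(0.36 × 0.64 + 0.24 × 0.76) / 125] = 0.0575
- (0.12 - 1.96 × 0.0580) / 0.0575 = 0.11, so power is 54%

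For 75 per arm at 60% v 40%:

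- SE₀ = √(2 × 0.50 × 0.50 / 75) = 0.0816
- SE₁ = √[(0.60 × 0.40 + 0.40 × 0.60) / 75] = 0.0800
- (0.20 - 1.96 × 0.0816) / 0.0800 = 0.50, so power is 69%

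With 60% v 45% instead, f = 40% gives a risk difference of 9 points, an NNT of 11.1, and power of 33% (all) v 45% (restricted).

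**The case against.** The strongest reply is that little depends on this analysis. Continuous outcomes go into a linear mixed model adjusted for baseline score and subgroup, and that model still runs when baselines are 0. The responder analyses come in addition, and the sample size rests on the Oswestry. Averaged over a mixed population, a smaller risk difference is also a true description of benefit per person treated. Effects are planned within each subgroup, including the one that requires leg symptoms. Finally, the coding of a zero baseline is often left to a statistical analysis plan, which is not shown here.

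Most of this stands and limits the severity. It does not remove the point. The article itself fixes the thresholds, the effect measures and an unrestricted population, and as written those rules make some people automatic failures and leave others unclassifiable. The subgroup analyses are acknowledged to be underpowered and do not change the overall responder definition.

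A reader might infer several stronger things that the documents do not support:

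- **That the 2-point risk ratio is diluted.** It is not: (1 - f) cancels and the ratio stays at 1.50.
- **That the 50% risk ratio would fall to 1.19 at f = 40%.** That figure, (0.40 + 0.36) / (0.40 + 0.24), needs every person in f to score 0 at both baseline and follow-up and to be coded a success. The article states no such coding, people scoring 1 have a defined reduction, and leg pain can begin during follow-up. It is an extreme case.
- **That one arm is favoured.** Baseline is recorded before randomisation, and allocation is stratified by subgroup, which is closely tied to leg symptoms. Only chance imbalance is expected.
- **That the main leg-pain estimate should be restricted to people with leg pain.** An effect confined to them would be averaged down in the mixed model (2 points becomes 2 × 0.6 = 1.2 at f = 40%). But replacing the all-randomised comparison in a self-described pragmatic trial changes the question and drops new leg pain. It is a trade-off, not a correction.
- **That the sciatica scales need the same rule.** They have no responder threshold and also cover numbness, tingling and weakness.

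**Conclusion.** The point holds for the responder analyses of the two pain scales, and mainly for leg pain. As written, a baseline of 0 or 1 is a built-in failure under the 2-point rule, and a baseline of 0 has no defined result under the 50% rule. The direction follows from the rules alone: for any f above zero and any true benefit, the risk difference shrinks by (1 - f) and the NNT rises by 1/(1 - f).

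The size is an illustration that depends on f and on the response rates, neither of which is in the documents. The 2-point calculation also takes f as equal in the two arms. An analysis plan that is not shown might add a restriction, but nothing in the article does.

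This should be fixed. It does not threaten the trial's main comparison, because the mixed model is unaffected by the undefined cases and the harm is dilution, lost power and an open coding choice.

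**What to change.** In Data analysis, define the 2-point and 50% responder analyses for each pain scale among participants with a baseline score of at least 2 on that same scale, and report the denominator by arm. Give the all-participant version as support, with a coding for baselines of 0 and 1 stated in advance.

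The questionnaire is sent before the initial examination and so precedes randomisation. Restricting on it keeps the comparison by allocated group. The value 2 is the severity floor already used for entry, applied to each scale.

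Keep the mixed model in all randomised participants as the main leg-pain analysis. A mean difference among those with baseline leg pain may be added as support only.

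The cost is a sentence or two of text and a smaller denominator for these additional analyses (75 instead of 125 per arm at f = 40%). For the 50% rule, the floor also leaves out people with a baseline of 1, whose reduction is defined. The supportive version covers them, and both rules then share one denominator.
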